### Monitoring data collection

All study team members will be trained by qualified, well-experienced professionals in areas referring to the planned measurements for the accurate performance of the procedures, data collection, and adherence to the study. Previously established procedures for data collection will be used (see Methods of Assessment section). The quality and correctness of the data collection will be checked by a researcher completing a structured online spreadsheet after each visit. Assessment of the electronic document will be performed once a week by a supervisor.

### Statistical analysis

Statistical analysis will be performed according to the E9 Statistical Principles for Clinical Trials [80]. For quantitative outcomes, the between-group comparisons will be performed using the ANOVA or Kruskal-Wallis rank-based nonparametric test depending on the data distribution followed by appropriate post-hoc tests. The qualitative outcomes will be compared using the Chi-square test. Longitudinal data will be analyzed with either repeated measures of ANOVA or aligned rank-transform ANOVA, depending on the data distribution, or McNemar’s test.

The analysis of the gut microbial community will include alpha diversity, beta diversity, ordination techniques (a principal coordinate analysis), and taxonomic and functional differences. Alpha diversity will be measured by means of the Chao1 (richness) and Shannon (richness and evenness) indices. All indices will be determined using originally observed count data (without data pre-processing) and comparison within the groups (V0–V3) and between the groups at the end of the study (at V3) using the non-parametric Wilcoxon signed-rank test or Mann-Whitney (or Kruskal-Wallis) test, respectively. Beta-diversity will be measured by means of the Bray-Curtis dissimilarity metric and the weighted UniFrac distance metric. Beta-diversity analysis will be preceded by the removal of rare species and normalization to account for unequal library sizes. The between-group differences in gut microbial composition will be visualized using principal coordinate analysis based on the Bray-Curtis dissimilarity and UniFrac distances. The permutational multivariate analysis of variance (PERMANOVA) will be conducted on the Bray-Curtis and weighted UniFrac dissimilarity matrices to assess the group-level (at V3) differences. Taxonomic differential abundance will be tested by comparing the fractional abundances. The analysis of alpha and beta diversity, ordination analysis, and taxonomic differential abundance will be conducted using the R (version 3.5.1) package Phyloseq [81]. The PERMANOVA+ add-on package of PRIMER 7 (version 7.0.13) will be used as analysis tools to compare beta diversity. To predict the metagenome functional content using the output of the 16S rRNA analysis pipeline, the software package PICRUSt will be used. Functional abundance differences will be analyzed and visualized using STAMP [82]. To account for multiple testing, FDR-adjusted *p* values (q values) will be reported.

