### Study population

A total of 120 adult volunteers with a diagnosis of major depressive disorder (MDD) will be recruited for this study. To be eligible in the trial, subjects must fulfil all of the inclusion criteria and none of the exclusion criteria, as stated below. The following inclusion criteria will be adopted:
Outpatients aged 18–60 years,Written informed consent to participate in this study before any study-mandated procedure,Meet the DSM-5 criteria for major depressive disorder (MDD) [42],Body mass index (BMI) ≥18.5 kg/m^2^ and ≤ 30 kg/m^2^,MADRS (Montgomery-Asberg Depression Scale) total score of 20 points or more (moderate or severe depression) at screening (V0) and at baseline (V1), andA willingness and motivation to follow the study protocol.

The exclusion criteria will be as follows:
Diagnosis of autoimmune, neurological, immunocompromised, thyroid, inflammatory bowel diseases, irritable bowel syndrome, diabetes, cancer, and/or IgE-dependent allergy;Psychiatric comorbidities (except specific personality disorder) including mental retardation, organic brain dysfunction, or addiction (except nicotine and caffeine);High risk of suicide in the investigator’s opinion;An infection one month before the study baseline visit (V1);The use of antibiotics and/or probiotics three months prior to the study;Glucocorticosteroids and/or metformin treatment;Dietary supplementation (except for vitamin D according to the “Vitamin D supplementation guidelines, 2018” [43]);Changes in a pharmacotherapy and/or psychotherapy of MDD 2 weeks before the trial entry;No specific (e.g. elimination, vegan, reduction) diet and changes in physical activity 4 weeks before the trial entry, andPregnancy or lactation.

Reasons for the participant to be discontinued from the study:
Withdrawal of informed consent,Lack or incomplete compliance with the diet and/or probiotic supplementation,Non-attendance at the study visits,Exclusion criteria found after enrollment, andAny serious adverse event during the intervention period (based on data safety monitoring).

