**Fig. 1 Fig1:**
[figure not shown]
Timeline of SANGUT STUDY visits. V0 – Screening visit; V1 – Baseline Visit; V2 – Visit 2; V3 – End of Study Visit

**Table 1 Tab1:** Schedule of study procedures

	Screening	Randomization	Intervention Period	End of the study
Visit Number	V0	V1	V2	V3
Visit time and Window	Day –7 to –1	Day 0	6 weeks ±3 days	12 weeks ±3 days
Informed consent	+			
Inclusion/exclusion criteria	+	+		
Somatic examination	+	+		
Neurological examination	+	+		
Socio-demographic characteristics	+			
Medical history	+			
Psychiatric history	+			
Depression symptoms severity	+	+	+	+
Stress level	+	+	+	+
Quality of life	+	+	+	+
Gastrointestinal symptoms	+	+	+	+
Dietary assessment	+	+	+	+
Physical activity	+	+	+	+
Anthropometric measures	+	+	+	+
Vital measures	+	+	+	+
Smoking status	+	+	+	+
Blood sample	+			+
Stool sample	+			+
Electroencephalography	+			+
Adverse events report		+	+	+

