### Data management and analysis plan

#### Data analysis principles

To evaluate the efficacy of the intervention on the well-being of patients, the following changes from the baseline (V1) to the end of the study (V3) will be determined as primary outcomes:
The severity of depression symptoms:
MADRS total scoreBDI total scoreThe severity of psychopathological impairment:
SCL-90 total scoreThe quality of life:
SF-36 total scoreStress levels:
PSS-10 total score

To evaluate the effect of the intervention on physiological parameters [79], the following changes will be determined as secondary outcomes:
In serum, from the screening (V0) to the end of the study (V3), levels of:
proinflammatory biomarkers: hs-CRP, Il-6, Il-1beta, and TNF-alphagluten sensitivity biomarkers: anti-TG2 IgG antibodies and anti-AGA IgG/IgA antibodiesintestinal permeability biomarkers: I-FABP/FABP-2 and LBPmetabolism biomarkers: total cholesterol, LDL cholesterol, HDL cholesterol, TG, glucose, and insulinHPA axis biomarker: cortisolliver function biomarkers: ALT and ASTIn stool, from the baseline (V1) to the end of the study (V3):
taxonomic and functional analysis of gut bacterial communitySCFAs levelsBrain activity, from the baseline (V1) to the end of the study (V3):
EEG analysisGastrointestinal symptoms, from the baseline (V1) to the end of the study (V3):
GSRS scale.

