To the best of our knowledge, this will be the first intervention study assessing the efficacy of both probiotic supplementation and a gluten-free diet and comparing the effect of both interventions and their combination in MDD patients. The protocol and the outline were developed by a multidisciplinary researcher team. The methodology employed in the study benefited greatly from our diverse set of knowledge, experience and perspectives. Considering the highly rigoristic selection criteria, the participant group is relatively large. Rigorous procedures established for this trial will be followed by well-trained researchers to ensure that research will be conducted in accordance with standards of best practice. The measurements listed above will be introduced to reduce the potential bias related to confounding variables (e.g. smoking, physical activity, and diet).

There may be some possible limitations in the design of the study:

First, the impossibility of blinding the diet is a factor that could affect assessment of both the participant and investigator. For this reason, the researcher evaluating the severity of symptoms will not be informed as to whether the patient will be allocated to the GFD or GD arm of intervention.

Second, the lack of motivation is a symptom commonly experienced by MDD patients and could contribute to the non-attendance at the study visits, incomplete implementation of the intervention, or failure to complete the intervention.

Third, patients in the GFD groups receiving dietary advice might try to introduce other changes in food consumption (e.g. reduce the food portion size and/or consume more vegetables and fruits). Therefore, health improvement may not be specific to the implemented gluten-free diet.

Finally, recall bias in self-reporting is another potential confounder of the study. However, dietary consultation and food intake assessment during the study period should minimize the likelihood of its occurrence.

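### The primary analysis is fixed on V1-to-V3 change with ANOVA-type tests, although drop-out is expected; in their usual complete-data form these make no use of V2 scores from patients without V3, and a mixed model would

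*Protocol article*

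**What the plan says.** Data analysis principles fixes the outcome for MADRS, BDI, SCL-90, SF-36 and PSS-10: "the following changes from the baseline (V1) to the end of the study (V3) will be determined as primary outcomes".

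Statistical analysis names the tests. For quantitative outcomes, "the between-group comparisons will be performed using the ANOVA or Kruskal-Wallis rank-based nonparametric test"; for repeated measurements, "Longitudinal data will be analyzed with either repeated measures of ANOVA or aligned rank-transform ANOVA", with the choice depending on the data distribution. The section also refers in general terms to the ICH E9 principles.

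Table 1 schedules V2 at six weeks. The row "Depression symptoms severity" is marked at all four visits, as are the rows for stress level and quality of life.

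The Discussion lists low motivation as a symptom common in this population, which "could contribute to the non-attendance at the study visits, incomplete implementation of the intervention, or failure to complete the intervention". Study population lists five reasons for discontinuation, among them "Lack or incomplete compliance with the diet and/or probiotic supplementation" and "Non-attendance at the study visits". The Discussion also concedes, of the open diet, "the impossibility of blinding the diet is a factor that could affect assessment of both the participant and investigator".

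**The concern.** A V1-to-V3 change does not exist for a patient without V3. ANOVA or Kruskal-Wallis on that change, and repeated-measures ANOVA in its classical form, therefore work from patients who have the scores they need. A patient assessed at V1 and V2 who then leaves adds nothing to the efficacy comparison, although the V2 score says a good deal about where V3 would probably have been.

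Two things are at stake. The first is precision, which is lost whatever the reason for leaving. The second is possible bias in the diet contrast. Only the GFD arms have to change what they eat, and the diet is open, so drop-out could be related to symptoms and unequal between diet arms. This is a choice of method that the article itself makes, and an analysis plan that follows its wording would inherit it.

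**Working it through.** **The plan's own figure.** The only figure given is about 81% power with 116 patients. With four measurements per patient and assumed f = 0.25, correlation 0.5 and alpha 0.05, the between-groups noncentrality is 0.25² × 116 × 4 / (1 + 3 × 0.5) = 11.6 on (3, 112) degrees of freedom. That gives 81.2%, so the figure is reproducible. It is not used further, because it concerns sample size and not the choice of method.

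**Inputs.** From the article: 120 patients in four arms of 30, hence 60 GFD against 60 GD; scores at V1, V2 and V3; outcome V3 − V1. Assumed, because the article gives none: MADRS SD 8 at each visit; correlations ρ12 = 0.5, ρ23 = 0.7, ρ13 = 0.4; no true effect; drop-out after V2 of 10–30%.

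**Precision under random drop-out.**

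- Variance of the change: 2 × 64 × (1 − 0.4) = 76.8.
- Regressing V3 on V1 and V2 gives standardised coefficients (0.4 − 0.5 × 0.7)/0.75 = 0.067 and (0.7 − 0.5 × 0.4)/0.75 = 0.667. R² = 0.4 × 0.067 + 0.7 × 0.667 = 0.493, and the residual variance is 64 × 0.507 = 32.43.
- With n randomised and k completers per arm, the variance of the contrast is 2 × 76.8/k for complete cases. With all V1 and V2 scores kept it is 2 × [(76.8 − 32.43)/n + 32.43/k] in large samples.

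| Drop-out in both arms | k | Complete-case SE | All-scores SE | Variance saved |
|---|---|---|---|---|
| 10% | 54 | √2.844 = 1.69 | √2.680 = 1.64 | 5.8% |
| 20% | 48 | √3.200 = 1.79 | √2.830 = 1.68 | 11.6% |

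Simulated trials under the same assumptions give SEs of 1.69 against 1.65 at 10% (variance saved 4.7%). At 20%, separate runs give 1.82 against 1.71 and 1.79 against 1.70 (10–11%).

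**Bias when drop-out depends on the V2 score.** With equal SDs, the regression slope of V3 − V1 on V2 is ρ23 − ρ12 = 0.2. The complete-case bias in an arm is 0.2 times the shift in mean V2 between that arm's completers and all its patients. Suppose drop-out is logistic in V2 with log-odds 1 per SD (assumed), and let z be standard normal with p(z) = 1/(1 + exp(−a − z)), where a sets the overall rate. The shift is 8 × E[z(1 − p(z))]/(1 − rate). Numerically this is −0.73, −1.39, −1.71 and −2.02 points at 10%, 20%, 25% and 30% loss.

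| GFD loss against 10% in GD | GD loss random | Same mechanism in both arms |
|---|---|---|
| 20% | 0.2 × (−1.39) = −0.28 | 0.2 × (−1.39 + 0.73) = −0.13 |
| 25% | −0.34 | −0.20 |
| 30% | −0.40 | −0.26 |

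Negative values favour GFD. The complete-case SE is √(76.8/48 + 76.8/54) = 1.74 at 20% and √(76.8/42 + 76.8/54) = 1.80 at 30%. The bias is thus between 0.13/1.74 = 0.08 and 0.40/1.80 = 0.22 SE. Equal or purely random loss gives about zero. The estimate that uses all V1 and V2 scores is within about 0.05 of zero throughout.

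**Range over other assumptions.** A different selection mechanism at SD 8 gave −0.39 to −0.53 (SE 1.73 to 1.81, so up to 0.29 SE). With SD 7 and about 25% against 10% loss, the bias was −0.16 to −0.28 when ρ23 − ρ12 = 0.2. It was −0.32 to −0.51 when ρ23 − ρ12 = 0.4, as the slope formula predicts. Only about 33% strongly symptom-related loss against 10% reached −0.51 to −0.97.

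**The case against.** The strongest reply is that the article names families of tests and leaves missing-data handling to an analysis plan that is not shown. Nothing in it says that patients without V3 are excluded, defines a complete-case population or rules out imputation. Aligned rank-transform ANOVA can also be fitted through a mixed model. This stands. A reader might infer that the plan drops every such patient; the documents do not support that, and the point holds only for the usual complete-data form of these tests without imputation. It survives as a point about the method named: the change score still needs V3, and a general reference to E9 does not alter the tests chosen.

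The harm is also modest. The article gives no drop-out rate and does not say that loss will differ by diet; low motivation is common to all arms. Even a bias of 0.3 SE raises the two-sided type I error only to about 6%. A reader might infer that the diet result will be biased, but that needs both symptom dependence and a difference between diet arms.

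Two further inferences should be resisted:

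- **A missed V2 alone.** A reader might say that a patient with V1 and V3 but no V2 is also lost. The change comparison keeps that patient, the article does not say which visits enter the repeated-measures model, and non-attendance is itself a listed reason for discontinuation.
- **The margin of 120 over 116.** This might be cited as proof of fragility. It is a separate sample-size matter, and a mixed model recovers only part of the lost information.

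**Conclusion.** The point holds in conditional form. Given the non-completion that the authors expect, the named methods in their usual complete-data form, without imputation, are a weaker choice than one that uses every collected score. The main cost is precision: about 10% of the information at 20% drop-out and about 5% at 10%. Bias in the GFD–GD contrast arises only if drop-out is symptom-related and unequal between diet arms. It is then about 0.1 to 0.5 MADRS points, at most about 0.3 SE, at 20–30% against 10% loss. All rates, SDs, correlations and drop-out mechanisms are assumptions. The bias scales with ρ23 − ρ12 and vanishes if those two correlations are equal. This is a worthwhile and cheap improvement, not a flaw that invalidates the trial.

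**What to change.** In Statistical analysis, make the primary analysis of the five scales a likelihood-based mixed model for repeated measures on V1, V2 and V3. It should have arm-by-visit terms, an unstructured covariance and all randomised patients with any available score. Estimate the between-arm difference in V1-to-V3 change from it, so that the outcome in Data analysis principles is unchanged. This replaces both the ANOVA on change and the repeated-measures ANOVA as primary. Keep the complete-case ANOVA or the rank-based tests as sensitivity analyses, including for clearly non-normal scores.

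Confirm that SCL-90 is taken at V2. Table 1 has no separate row for it, and without a V2 score the gain for that scale is smaller.

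The cost is a change of wording and a standard procedure in R, which the team already uses for the microbiota analysis; no new data are needed. The model relies on missingness being explained by observed scores. That is a weaker assumption than complete-case analysis needs, but neither analysis protects against drop-out driven by the unobserved V3 score.

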**Methods:**

A total of 120 outpatients will be equally allocated into one of four groups: (1) probiotic supplementation+gluten-free diet group (PRO-GFD), (2) placebo supplementation+ gluten-free diet group (PLA-GFD), (3) probiotic supplementation+ gluten containing diet group (PRO-GD), and (4) placebo supplementation+gluten containing diet group (PLA-GD). PRO groups will receive a mixture of psychobiotics (*Lactobacillus helveticus* R0052 and *Bifidobacterium longum* R0175), and GFD groups will follow a gluten-free diet. The intervention will last 12 weeks. The primary outcome measure is change in wellbeing, whereas the secondary outcome measures include physiological parameters.

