### Sample size calculation

Based on the results of other studies evaluating probiotic strains that will be used in the present study, we assume that the mean effect of intervention will be of a medium size. As the primary outcomes will be repeatedly measured and four groups of patients will be entering the trial, there will be an approximately 81% probability of correctly rejecting the null hypothesis of no difference between the study groups with a total of 116 patients.

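### The observed distribution picks the test for the primary scales, and one permitted branch, the aligned rank-transform group-by-time test, can exceed 5% type I error when V3 scores are much more spread than V1 scores

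*Protocol article*

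**What the plan says.** The Statistical analysis section of the protocol article gives two conditional rules. For quantitative outcomes, "the between-group comparisons will be performed using the ANOVA or Kruskal-Wallis rank-based nonparametric test depending on the data distribution", with post-hoc tests to follow. For repeated data, "Longitudinal data will be analyzed with either repeated measures of ANOVA or aligned rank-transform ANOVA, depending on the data distribution".

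The Data analysis principles section states that "the following changes from the baseline (V1) to the end of the study (V3) will be determined as primary outcomes" and lists five total scores: MADRS, BDI, SCL-90, SF-36 and PSS-10. The Sample size calculation section describes the primary outcomes as repeatedly measured. A primary scale can therefore fall under both rules, and the article does not say which result decides.

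The Study population section requires a MADRS "total score of 20 points or more (moderate or severe depression) at screening (V0) and at baseline (V1"). No other primary scale has an entry threshold. The article gives no mean, SD or between-visit correlation for any scale.

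**The concern.** The test for a primary outcome should be fixed before the outcome data are seen. Here the choice between a mean-based and a rank-based test waits for the data, and two families of test can be run on the same scale.

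This would matter less if every permitted branch held its error rate. The aligned rank-transform branch may not. It removes the estimated main effects, adds back the estimated interaction and ranks all visits together. With two visits the estimated interaction is split equally between them. If V1 values are tightly packed and V3 values widely spread, the share placed on V1 moves many ranks, although most of the noise came from V3. The ordinary two-visit group-by-time test is the same as ANOVA on the within-patient change, so unequal visit spread does not harm it.

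At stake are the false-positive rate on a primary scale, the possibility of two p values for one outcome, and, in the rank branch, a result with no effect in scale points. MADRS deserves particular attention because its V1 distribution is cut at 20 by design and its V3 distribution is not.

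**Working it through.** **The plan's own figure.** The only operating characteristic stated is power: "approximately 81% probability of correctly rejecting the null hypothesis of no difference between the study groups with a total of 116 patients". Assume that a medium effect means f = 0.25, with four measurements (V0 to V3 in Table 1), correlation 0.5 and two-sided alpha 0.05. The between-group noncentrality is then f² × N × m / (1 + (m − 1)ρ) = 0.0625 × 116 × 4 / 2.5 = 11.6. On 3 and 112 degrees of freedom this gives power 0.812, which matches. It concerns a mean-based F test and says nothing about type I error. No type I error is stated for any branch, so it has to be simulated.

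**Inputs from the article.** Four arms of 30; MADRS of at least 20 at V0 and V1; the four named tests; primary outcome V1-to-V3 change.

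**Assumed inputs.** Two-sided 5%; integer MADRS scores; before the cut, V1 mean 24 and SD 6, visit correlation 0.5, mean drop 10 points in every arm; pre-cut V3 SD varied from 5 to 11. There were 6,000 trials per row, so the standard error at 5% is √(0.05 × 0.95 / 6,000), about 0.3 points.

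**Rejection rate of the group-by-time test with no effect**

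| SD at V1 | SD at V3 | Ratio | Aligned rank, V1/V3 | Aligned rank, V1/V2/V3 | Repeated-measures ANOVA, V1/V3 |
|---|---|---|---|---|---|
| 4.40 | 4.63 | 1.05 | 5.0% | 5.2% | 5.2% |
| 4.41 | 5.53 | 1.26 | 5.6% | 5.3% | 5.1% |
| 4.40 | 6.44 | 1.46 | 7.4% | 7.0% | 5.8% |
| 4.40 | 7.30 | 1.66 | 8.5% | 7.1% | 5.0% |
| 4.41 | 8.15 | 1.85 | 10.3% | 8.8% | 5.4% |
| 4.41 | 8.97 | 2.03 | 11.7% | 9.6% | 4.9% |
| 4.40 | 9.77 | 2.22 | 13.7% | 10.3% | 4.8% |

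A separate simulation of the same set-up gave 5.9%, 6.8%, 8.8% and 10.0% for the aligned rank test at ratios 1.26, 1.46, 1.66 and 1.86. There, ANOVA on change, Kruskal-Wallis on change and the baseline-adjusted model all lay between 4.4% and 5.4%. Across a wider set of assumptions (pre-cut V1 mean 20-28, correlation 0.3-0.7), ANOVA on change gave 3.5-6.0% and Kruskal-Wallis on change 3.8-5.7%.

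**What drives the excess.** Two comparisons separate the entry cut from unequal spread:
- Cut present, equal pre-cut SDs (second row, 6 and 6): the cut alone produces a ratio of 1.26, and the error is 5.3-5.6%.
- No effective cut: at ratio 2.00 the error is 12.0% (two visits) and 9.1% (three visits); at ratio 1.00 it is 4.6% and 5.3%.

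Unequal spread between visits is therefore the main cause. The cut contributes by narrowing V1.

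**Would MADRS reach the rank branch?** The article names no normality check. With Shapiro-Wilk at 5% as an assumed check, the share of trials failing depends on what is checked:

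| Quantity checked | Trials failing |
|---|---|
| Raw V1 scores, pooled (n = 120) | 76-100% |
| Raw V1 scores, at least one of four arms | 44-95% |
| Raw V1 scores, one given arm (n = 30) | 13-54% |
| V1-to-V3 changes | 5-16% |
| Model residuals | 4-6% |

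If the pooled V1 check selects the longitudinal test, the overall error across these scenarios is 5.2-11.2%.

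**The case against.** The strongest reply is that the primary outcome is a change, one value per patient, and so belongs under the between-group rule. Both tests named there hold about 5%. The longitudinal sentence could be meant for trajectories across visits, and an analysis plan that is not shown may say which result decides and how the distribution is judged. Much of this stands. The missing normality criterion is no finding in a condensed article, and choosing between ANOVA and Kruskal-Wallis on change does little harm to the error rate. What remains is the stated text: it makes the test depend on the data and admits the aligned rank-transform test for repeatedly measured primary scales.

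A reader might also draw three stronger conclusions, which the document does not support:
- That the error rate on MADRS is 7-11%. This needs a V3 SD about 1.4-2.0 times the V1 SD, and the article gives no SD. At ratios up to about 1.3 the rate is near nominal.
- That the entry threshold steers MADRS into the rank branch and causes the inflation. Steering is likely if pooled raw V1 scores are checked, but uncommon for changes or residuals, which are closer to what ANOVA assumes. The inflation also appears with no cut at all. The threshold applies to none of the other four scales.
- That success would be claimed on whichever test rejects. The article never says so.

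**Conclusion.** The point holds in limited form. The data-dependent choice and the overlap of the two rules concern all five primary scales. The error-rate consequence is confined to the aligned rank-transform branch and depends on the ratio of V3 to V1 spread: about 5-6% up to a ratio of 1.3, 7-9% at 1.5-1.7 and 10-12% at 1.9-2.0. These figures rest on assumed means, SDs and a correlation of 0.5. A ratio above 1.4 is plausible for MADRS, since entry restricts the V1 range while V3 mixes patients who improve with patients who do not, but the document does not establish it. The text should be changed because one permitted route can lose error control while simpler alternatives keep it.

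**What to change.** In the Statistical analysis section, for the five primary outcomes, remove the condition on the data distribution and name one deciding analysis: a linear model of the V3 score on randomised group with the V1 score as covariate, reporting group differences in scale points with 95% confidence intervals. Modelling the V1-to-V3 change with the same covariate gives identical group differences, so the stated primary outcome is kept. State that Kruskal-Wallis, repeated-measures ANOVA and aligned rank-transform ANOVA are sensitivity analyses that cannot replace it.

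The cost is a wording change, with no effect on visits, data or sample size. The downside is a small loss of efficiency if a score is strongly skewed, and the retained rank analyses would show whether that matters.

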#### Stool collection

Participants will be asked to collect stool samples after overnight fasting to avoid the effect of food consumption on short-chain fatty acid synthesis. Each participant will receive detailed instructions describing the method for material collection. A plastic holder will be used to collect faeces into a sterilized screw-capped collection container. Participants will be asked to store the sample in a fridge and deliver the sample up to 24 h after collection to the clinic. The samples will be preserved in 2 mL Eppendorf tubes containing 600 μL DNA/RNA later solution (Zymo Research, Freiburg, Germany) to prevent the degradation processes and will be frozen at − 80 °C until the beginning of the microbiota analyses.

DNA extracted from the stool will be amplified using primers flanking the hypervariable region of the 16S rRNA gene. 16S amplicons will be sequenced using an Illumina MiSeq platform (Illumina Inc., San Diego, CA, USA) and the raw reads will be processed using the Mothur pipeline (version 1.39.5) [76]. The SILVA 132 rRNA database [77] will be used to assign taxonomy. To predict a microbial community metagenome and its functional potential based on the 16S data, the PICRUSt software package will be used [78].

An overview of the study design and assessments to be conducted during the study and their timing is presented in Fig. 1 (study design) and Table 1 (assessment point times and examined variables).

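### Chao1 richness is fixed on raw counts with no adjustment for sequencing depth, so the within-arm V0–V3 test can show a false change if mean depth differs between visits

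*Protocol article*

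**What the plan says.** The Statistical analysis section names the indices: "Alpha diversity will be measured by means of the Chao1 (richness) and Shannon (richness and evenness) indices". On the data that feed them it says "All indices will be determined using originally observed count data (without data pre-processing". Each index is compared within arms from V0 to V3 and between arms at V3, "using the non-parametric Wilcoxon signed-rank test or Mann-Whitney (or Kruskal-Wallis) test, respectively".

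The other microbiota analyses in that section do scale for depth. For beta diversity, "Beta-diversity analysis will be preceded by the removal of rare species and normalization to account for unequal library sizes". For single taxa, "Taxonomic differential abundance will be tested by comparing the fractional abundances".

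On the laboratory side, the Stool collection section says "16S amplicons will be sequenced using an Illumina MiSeq platform" and that samples stay frozen "until the beginning of the microbiota analyses". It gives no target depth, no minimum read count and no allocation of samples to runs.

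Under Data analysis principles, the taxonomic and functional analysis of the gut bacterial community is a secondary outcome. Chao1 is not listed there by name; it is one index within that analysis.

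**The concern.** The section recognises that library sizes will be unequal and deals with this for beta diversity and, through fractional abundances, for taxa. It does not do so for alpha diversity, which holds the one richness index and the one most sensitive to depth. Not filtering rare taxa and not equalising depth are two separate decisions, and the instruction to leave counts unprocessed covers both. Chao1 needs the singletons and doubletons, which is a good reason for the first decision but not for the second.

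At stake is the reading of a richness change within an arm. If the V3 samples were on average read more deeply than the V0 samples, Chao1 would rise from V0 to V3 with no change in the gut community. The planned signed-rank test cannot tell the two apart, and the FDR adjustment deals with multiplicity, not bias.

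**Working it through.** **Inputs.** From the article: raw counts, the two indices, the rank tests, and 120/4 = 30 patients per arm ("A total of 120 outpatients will be equally allocated into one of four groups"). The article gives no alpha diversity figure to reproduce, and no depth, number of taxa or run layout. The following are therefore assumptions: log-normal abundances with log SD 2 to 3, 300 to 1,000 taxa, multinomial reads, 5,000 to 80,000 reads per sample, depth CV 0.3 or 0.6, and a mean depth ratio of 1 to 2.

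**Step 1: does Chao1 depend on depth?** Formula: Chao1 = S_obs + f1(f1 − 1)/(2(f2 + 1)), where S_obs is the number of taxa seen, f1 the singletons and f2 the doubletons. Means for 500 taxa, log SD 2.5:

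| Reads | S_obs | Chao1 | Step per doubling |
|---|---|---|---|
| 5,000 | 238.0 | 311.9 | |
| 10,000 | 287.6 | 354.4 | +42.5 |
| 20,000 | 332.0 | 390.4 | +36.0 |
| 40,000 | 379.4 | 424.9 | +34.5 |
| 80,000 | 413.8 | 447.5 | +22.6 |

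The true richness is 500, so even at 80,000 reads the estimate reaches 447.5/500 = 89.5% of it.

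Going from 10,000 to 20,000 reads in other settings:
- 400 taxa, log SD 2: 352 to 370, +5.1%
- 800 taxa, log SD 3: 396 to 454, +14.6%
- 300 taxa, log SD 2: 270.7 to 282.4, +4.3%
- 1,000 taxa, log SD 3: 465.8 to 538.4, +15.6%

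That is about 5 to 15%. From 40,000 to 80,000 reads the rise is smaller in each setting: +1.4% (300 taxa, log SD 2), +5.3% (500, 2.5) and +11.9% (1,000, 3).

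Shannon for 800 taxa, log SD 2.5 is 3.911, 3.935 and 3.949 at 5,000, 10,000 and 20,000 reads. That is +1.0% over a fourfold rise in depth.

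**Step 2: what does this do to the planned tests?** Setting: 500 taxa, log SD 2.5, mean depth 20,000 reads in the lower-depth set, 30 per arm, no systematic community change, two-sided 0.05. Share of null trials in which raw Chao1 is declared different:

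| Mean depth ratio | Paired V0–V3, CV 0.3 | Paired V0–V3, CV 0.6 | Two arms at V3, CV 0.3 |
|---|---|---|---|
| 1.0 | 6.0% | 6.8% | 2.7% |
| 1.1 | 9.3% | 11.5% | not run |
| 1.25 | 36.5% | 17.5% | 25.7% |
| 1.5 | 82.5% | 52.8% | 61.3% |
| 2.0 | 99.8% | 96.3% | 96.3% |

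The paired columns use 400 trials per cell and the last column 300, so the error around a true 5% is about ±2 to ±2.5 points. In the last column the ratio is between the two arms, not between visits. The mean false difference in the paired test at CV 0.3 is +19.8 taxa at ratio 1.5 and +32.8 at ratio 2. Shannon stayed between 3% and 7% throughout.

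**Step 3: does equalising depth remove it?** Rarefying the same unfiltered counts to the smallest library (CV 0.3, 300 trials) gave paired rejection rates of 8%, 6% and 7% at ratios 1, 1.5 and 2, and a mean false difference of about 0 taxa.

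**Step 4: what if depth varies only at random?** The error rate stays near nominal (first row of the table). Power of the V3 Mann-Whitney test, raw counts against repeated rarefaction averaged over 10 draws (200 trials, error about 3.5 points), with an assumed SD of true richness of 50 or 125:
- CV 0.3: 66.5% against 66.5%, and 64.5% against 66%
- CV 0.6: 56% against 60.5%, and 66% against 66.5%

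The gain is 0 to 4.5 points, mostly within simulation error.

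**The case against.** The strongest reply is that the harm needs a condition the article does not state. With equal mean depth the tests hold their level. Storage of frozen samples until analysis fits one batch at least as well as separate runs per visit, and an article may leave run layout to the full protocol. This stands: the documents support saying that a false change can occur, not that it will.

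A reader might also infer that the randomised comparison at V3 is biased. The documents do not support that. If V0 and V3 went on different runs, V3 depth would shift alike in all four arms. Every patient is randomised at V1 and seen at 12 weeks, so nothing in the design staggers the arms. The exposed test is the within-arm one, which could not establish a treatment effect by itself anyway.

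Nor is the different handling of alpha and beta diversity a contradiction. The two need different preparation, and Chao1 on observed counts is a coherent choice. Replacing raw counts outright by rarefaction is debated: it discards reads, and in one check a single rarefaction had slightly less power than raw counts (60% against 65.6%).

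It might be said that the phrase on pre-processing means only that rare taxa are kept. Even so, nothing else stated for alpha diversity adjusts for depth. What remains after these points is an unguarded route to bias that is cheap to close.

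**Conclusion.** The point holds as a minor one. The written rule leaves Chao1 dependent on depth: about 5 to 15% from 10,000 to 20,000 reads, and less at higher depth. The planned tests cannot correct for this. A systematic difference in mean depth between V0 and V3 of 1.25 to 1.5 would give a false within-arm change in roughly 18 to 83% of null trials. The V3 comparison between arms is affected only if depth differs by arm, and random depth variation costs little. All these sizes rest on assumed depths, communities and depth ratios, because the article gives none. Shannon is practically unaffected, beta diversity and taxon comparisons are already scaled, and no primary outcome is touched.

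**What to change.** Keep the counts unfiltered, with singletons retained, and keep the raw-count Chao1 if wanted. Add one depth-adjusted Chao1 analysis:
- Chao1 at one common depth, by repeated rarefaction of the unfiltered counts, averaged over draws; or
- a model with log library size as covariate: within arms, the change in Chao1 on the change in log library size; at V3, arm plus log library size. The roughly even steps per doubling in the table above make the log scale reasonable.

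State that a richness change will be claimed only if it holds after depth adjustment. Where practical, put each patient's V0 and V3 samples in the same run, with arms mixed across runs.

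The cost is a few lines of code and a plate layout. The downside is that samples below the common depth drop out of the rarefied comparison. The covariate analysis on raw counts keeps them, so it is sensible to report both.
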